## Abstract

**Background::**

Delirium is a severe neuropsychiatric clinical state presenting as an acute onset of cognitive deficits. Patients receiving invasive mechanical ventilation (IMV), have the highest incidence (50%–80%) of delirium amongst patients admitted to intensive care units. Preliminary data indicates that early mobilisation is associated with reduced delirium in critically ill patients. However, definitive evidence is lacking. Current practice varies due to many barriers to patients, who require IMV, receiving early mobilisation interventions. In-bed cycling may address some of these barriers. This research aims to evaluate the feasibility and acceptability of early in-bed cycling to reduce delirium in critically ill patients.

**Methods::**

This multi-site feasibility randomised controlled trial will evaluate early (⩽48 h following IMV), in-bed cycling as a method of early mobilisation, to reduce delirium. Eighty-four participants will be randomised across three sites in a 1:1 ratio, to receive either early in-bed cycling in addition to usual care or usual care alone. The primary outcome is feasibility (recruitment, retention, intervention fidelity). Secondary outcomes include different methods of measuring delirium, physical function, length of stay, ventilator free days, sedation free days, Richmond Agitation Sedation Scale, adverse events and mortality. Descriptive statistical analyses will be conducted. Hypothesis testing will be used for exploratory analysis of the mechanistic sub-study outcomes. An embedded qualitative interview study will evaluate the acceptability of this research.

**Conclusion::**

This trial has been prospectively registered (ISRCTN74277350) and received full ethical approval (REC reference: 24/SC/0096). The trial opened to recruitment in July 2024. Recruitment will take place across 18-months.

## Background

Delirium is a prevalent and serious neuropsychiatric condition in critical care settings, associated with significant morbidity and mortality.^
1
^ It is defined as a severe neuropsychiatric clinical state presenting as an acute onset of cognitive deficits for example, inattention, fluctuant levels of consciousness from near-coma to severe agitation and psychotic episodes.^2–4^ Among intensive care unit (ICU) patients, those receiving invasive mechanical ventilation (IMV) exhibit the highest incidence of delirium (50%–80%).^2,5^ From 2022 to 2023, there were 189,141 ICU admissions in the UK, and of these 80,902 patients (43%) received IMV within 24-h of admission.^
6
^ Delirium is associated with long-term cognitive impairment, poor memory, hallucinations, attention difficulties and poor quality of life (QoL) following discharge from the ICU.^
7
^ Moreover, a systematic review estimated the substantial economic costs associated with delirium.^
8
^ Findings suggested that costs were increased by 52% when the development of long-term cognitive impairment as a consequence of delirium was considered. Identifying the causal mechanisms of delirium are challenging due to the number of precipitating (sedation, immobility) and predisposing (age, co-morbidities) factors for the development of delirium.^2,9^ The cerebral metabolic insufficiency hypothesis and severe systemic inflammation have been proposed as plausible theories.^
2
^ These describe biological mechanisms leading to acute brain dysfunction and thus, the development of delirium. Best practice guidelines suggest a bundle of care involving pharmacological and non-pharmacological interventions (including early mobilisation interventions) to prevent and manage delirium.^
10
^ There is no standardised definition of early mobilisation. However, mobilisation is described as ‘a type of intervention within rehabilitation that facilitates the movement of patients and expends energy with a goal of improving patient outcomes’.^
11
^ A recent systematic review and meta-analysis investigated if early mobilisation as a stand-alone intervention or as part of a bundle, prevented or reduced delirium in critically ill patients.^
12
^ Results showed that early mobilisation as part of a care bundle reduced the risk of delirium by 47% and reduced delirium duration by 1.8 days. There was significant variation of results between trials investigating out-of-bed mobilisation interventions and no significant results for early mobilisation as a stand-alone intervention. However, there was a high level of uncertainty and heterogeneity of interventions and populations. Only six included studies investigated early mobilisation as a stand-alone intervention. Of these, two (one randomised controlled trial, one feasibility trial) included delirium as a primary outcome and neither were sufficiently powered. Many barriers exist to implementing early mobilisation interventions for patients requiring IMV.^
13
^ In-bed cycling may address barriers such as IMV to mobilising critically ill patients.^
14
^ However, further evidence is needed to investigate the effectiveness of the intervention as a stand-alone method of early mobilisation.^14,16^ Public advisory group (PAG) members, with experience of delirium and early mobilisation in the ICU (previous patients and relatives), reported that in-bed cycling may improve implementation of early mobilisation for patients receiving IMV, because it can be delivered in bed. Moreover, the public representatives highlighted the value of understanding the experience of in-bed cycling from the perspective of patients, relatives and/or carers.

## Aim

The aim of the FRECycl-D trial is to evaluate the feasibility and acceptability of early (⩽48 h following IMV), in-bed cycling as a method of mobilisation, to reduce delirium in the ICU.

### Trial design

A multi-site feasibility randomised controlled trial (RCT) with an embedded qualitative interview study and mechanistic sub-study. The qualitative interview study and mechanistic sub-study will be detailed in their respective protocols.

## Methods

The SPIRIT checklist (2013) has informed the development of this protocol.^
17
^ A previous systematic review investigating in-bed cycling as a method of early mobilisation in the ICU guided the development of the in-bed cycling protocol.^
18
^ The relevant core outcome sets (COS) have guided the selected delirium outcomes and functional outcome measures.^19,20^ The embedded qualitative study will be reported separately. It will inform the trial evaluation including the acceptability of this research from the perspectives of the key stakeholders.

### Setting

Adult patients receiving IMV on ICUs will be recruited into the FRECycl-D trial across three sites:

University Hospitals Plymouth NHS Trust, Derriford.Torbay and South Devon NHS Foundation Trust, Torbay.Blackpool Teaching Hospitals NHS Foundation Trust.

### Participants

Eighty-four adult patients who meet the eligibility criteria will be enrolled into the trial within 48-h of IMV being initiated. Eligibility criteria were decided upon in consultation with expert recommendations, the research team and reference to similar trials to optimise comparability of findings. Electively admitted patients were not included due to their known predicted shorter ICU stay. Following review of the site Intensive Care National Audit and Research Centre quarterly reports, discussion with the site teams, trial steering committee and regional network recommendations, the inclusion criterion, expected to remain on IMV, was revised (Table s1, Supplemental File).

#### Inclusion criteria

Adults (aged ⩾ 18 years)Unplanned ICU admissionsIMV initiated ⩽ 48 h after ICU admissionExpected to remain on IMV > 24 h (amended from >72 h)

#### Exclusion criteria

Contraindications to mobilisationKnown or suspected cognitive impairment and/or learning difficultiesPlan is for palliation/withdrawal of treatmentImmobile prior to ICU admissionBody weight over the device safety limit (⩾135 kg)BMI < 18.5 kg/m^2^Planned ICU admissionPregnancyPrisoners

### Randomisation

Following written informed consent or consultee agreement, eligible participants will be randomised using permuted block-randomisation, stratified to site, in a 1:1 ratio, to either the intervention or comparator group. The randomisation module in REDCap provided by the Peninsula Clinical Trials Unit (PenCTU) will be used.

#### Intervention

Participants in the intervention group will receive in-bed cycling 5 days per week for a maximum of 14-days from randomisation or until out-of-bed mobilisation commences (whichever comes first). The delivery (days) of the intervention was decided upon in consultation with members of the research team with consideration of available resources and NIHR award collaborators who represent diverse professions and experience in critical care (see Figure 1 below and Figure s1 for details). The intervention will be in addition to usual care. The chief investigator/site physiotherapist/ICU rehabilitation team member at each site will deliver the intervention using an in-bed cycling device (MOTOmed, CE marked with class II medical device status and used as per intended purpose). A safety assessment will be conducted each day prior to commencing the in-bed cycling protocol (Tables s2–s6). The safety assessment has been informed by an international consensus of recommendations for mobilising patients receiving IMV in the ICU.^
21
^ The recommendations consider in-bed and out-of-bed safety criteria across four categories: neurological, respiratory, cardiovascular and other criteria. These were reviewed by, and agreed upon, with two local expert advisors (DM, RB). The in-bed cycling protocol and intervention safety criteria are described in detail in the Supplemental Material.

**Figure 1. fig1-17511437251400612:**
[figure not shown]
In-bed cycling protocol.

#### Comparator

Usual care only. Early mobilisation initiated within 4 days of ICU admission is unusual in UK ICUs. Generally, non-cycling exercise is initiated in patients receiving IMV for example, assisted-limb movement. Currently, the participating sites do not use in-bed cycling within 48-h of IMV.

All participating sites will follow and record a targeted sedation protocol for the intervention and comparator group using the Richmond Agitation Sedation Score (RASS −4 to +2) to minimise confounding factors.

### Outcomes

#### Primary outcomes

The following measures will be collected to determine trial feasibility:

Recruitment rate (% of participants enrolled vs participants eligible),Retention rate (% of enrolled participants who completed the intervention protocol in full excluding deaths),Intervention fidelity (% intervention sessions completed in full).The acceptability of the intervention will be evaluated by the key stakeholders (assessed by qualitative interviews). The protocol for this will be published separately.

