### Follow-up

All trial participants will be followed up at 90-days from randomisation. Participants will complete questionnaires measuring quality of life (QoL) and pain (EQ-5D-5L, SF-36), a cognitive screening assessment (MOCA) and assessment of their physical function (6MWT). Their relatives and/or carers will complete a proxy QoL questionnaire (proxy-EQ-5D-5L) and an assessment for the presence of delirium (FAM-CAM).

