### Statistical plan

#### Sample size

The aim of the study is to provide estimated rates of feasibility outcomes (recruitment, retention, fidelity). For a feasibility RCT designed with 80% power and one-sided 5% alpha, a sample size of 58 participants (29 per treatment arm) is recommended.^
22
^ Eighty-four participants will be recruited (42 per group). This will allow for a loss to follow-up due to mortality (up to 30%).^
6
^ This number is based upon recruitment uptake, participant retention and intervention fidelity using a red, amber, green (RAG) system as per best practice guidelines (Table s8) and in consultation with the PenCTU and expert opinion (VA, DM).^
22
^ The RAG system will guide progression to a definitive trial of effectiveness where green (go) and amber (go with changes made) criteria are met. If feasibility criteria are within the red, this means progression to a full trial will only be considered if changes are possible. The RAG criteria have been pre-defined in consultation with expert opinion and will be consulted across the length of the feasibility trial by the key stakeholders (Chief Investigator, PIs, PenCTU, Sponsor, Trial Steering Committee and Trial Management Group).^
23
^ This estimated sample size aims to ensure all areas of uncertainty that is, feasibility measures, are tested and an appropriate sample population for the qualitative study and mechanistic sub-study is achieved.

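### The primary retention rate counts completion of the cycling protocol, which usual-care participants do not have, so it is capped near 50% or rests on one arm, and it leaves day-30 and day-90 losses out of the progression criteria

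*Protocol article*

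**What the plan says.** Under Outcomes, Primary outcomes, the protocol article lists three numerical feasibility rates: recruitment, retention and fidelity. Retention is "Retention rate (% of enrolled participants who completed the intervention protocol in full excluding deaths". Fidelity is "Intervention fidelity (% intervention sessions completed in full".

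The Randomisation section allocates participants "in a 1:1 ratio, to either the intervention or comparator group". The Intervention section reserves cycling for one arm: "Participants in the intervention group will receive in-bed cycling 5 days per week for a maximum of 14-days from randomisation", ending sooner if out-of-bed mobilisation begins. The Comparator section reads "Usual care only".

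The Follow-up section states: "All trial participants will be followed up at 90-days from randomisation". Secondary outcomes include delirium at day 30 in both arms.

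The Sample size section names retention as one of the rates the study exists to estimate and as an input to the red-amber-green progression decision (thresholds in Table s8, not shown). The only loss to follow-up it allows for is mortality, up to 30%.

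**The concern.** The numerator and denominator of the retention rate come from different populations. The denominator is everyone enrolled, a term the Participants section uses for all 84. The numerator can be reached only by people assigned to cycling.

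The construct is also wrong for the label. A retention rate should say how many participants stay in the trial and supply outcome data. This one says how many finish a treatment course of at most 14 days. Loss from a 90-day follow-up, in either arm, does not enter it.

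At stake is the usefulness of one of the three rates that guide progression. A committee reading this figure could judge retention poor because usual-care participants were counted as failures, or good because later dropout was never counted.

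**Working it through.** **1. Reproduce the plan's total.** The Sample size section starts from 58: "a sample size of 58 participants (29 per treatment arm) is recommended". With 30% loss, 29 / (1 − 0.30) = 41.4, rounded up to 42 per arm, or 84 in total. This agrees with the plan. The base of 58 ("designed with 80% power and one-sided 5% alpha") cannot be rebuilt, because the Table s8 thresholds are not shown.

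**2. Ceiling with all enrolled participants in the denominator.** Suppose every surviving cycling participant completes. Deaths are taken out of both numerator and denominator.
- No deaths: 42 / 84 = 50%.
- 30% deaths in each arm: 42 × 0.70 = 29.4, about 29 alive per arm, so 29 / (29 + 29) = 29/58 = 50%.
- Unequal mortality moves the cap but does not remove it. With 30% deaths in one arm and none in the other, it is 29/71 = 41% or 42/71 = 59%.

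**3. Precision if the denominator is the cycling arm only.** The rate then rests on 29 to 42 people. The 95% half-width is 1.96 × √[p(1 − p)/n], with p = 0.80 as an assumption:

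| Basis | n | Half-width (points) |
|---|---|---|
| Cycling arm, survivors at 30% mortality | 29 | ±14.6 |
| Cycling arm, all | 42 | ±12.1 |
| Both arms, survivors at 30% mortality | 58 | ±10.3 |
| Both arms, all | 84 | ±8.6 |

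**4. What the rate records.** Three hypothetical survivors:

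| Participant | Printed retention rate | In the trial to day 90? |
|---|---|---|
| Usual care, every assessment supplied | Cannot count as retained | Yes |
| Cycling, protocol finished, lost before day 30 | Retained | No |
| Cycling, gives up cycling partway, every assessment supplied | Not retained | Yes |

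Withdrawal from the cycling arm during the treatment period would register, but only as non-completion, mixed with stopping cycling for other reasons. Withdrawal from usual care, or from either arm after cycling has ended, registers in none of the three rates. Recruitment concerns entry and fidelity concerns sessions. The Consent sections make later withdrawal a real possibility: a consultee is told that the participant can leave at any point, and consent is sought again if capacity returns.

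**The case against.** The best defence is that readers will understand retention to mean the cycling arm, and that Table s8 or the separate analysis plan may say so. That reading removes the 50% cap, so a wrong number is not certain. But the printed text says enrolled participants, and restricting it to one arm still leaves usual-care loss and day-90 loss uncounted. Another defence is that the phrase means each arm's allocated care. The article describes a cycling protocol and, for both arms, a sedation protocol; it gives no protocol that a usual-care participant could complete as an intervention.

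Four stronger readings are tempting and are not supported:

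- *Retention duplicates fidelity.* The units differ: participant against session. Both concern adherence, so they overlap, but they are not the same number.
- *One missed session makes a participant not retained, so the rate would collapse.* With ten sessions, each completed independently with probability 0.90, 0.90^10 = 0.35 would complete all of them. That requires *in full* to mean every session. The article does not say so, and staying on the protocol until its defined end is an equally available reading. Ten sessions (5 × 2 weeks) is also a maximum.
- *The trial cannot show differential loss between arms.* The Analysis of outcomes section promises CONSORT participant flow and missing data presented by group. Losses by arm should be visible there. They are simply not the named progression criterion.
- *The rate would set the attrition allowance of the definitive trial.* The Sample size section ties it to progression only, and even a red result leaves progression open if changes are possible.

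**Conclusion.** The definition is wrong as printed for a two-arm trial. It is either capped at about 50% (exactly so with equal arms and equal mortality) or confined to 29 to 42 people in one arm. On both readings it measures adherence to cycling, and no feasibility rate feeding the progression decision counts withdrawal or non-attendance at day 30 or day 90 in either arm.

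The cap assumes the literal denominator. The precision figures assume a true rate of 80%, and the lower sample sizes assume the plan's 30% mortality in each arm. The construct problem needs none of these assumptions. Table s8 and the analysis plan were not available. If they define retention differently, the published primary outcome disagrees with them and needs correcting all the same.

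**What to change.** - Define retention, by arm and overall, as participants providing the key outcome data at named time points (for example day 30 and day 90) divided by randomised participants alive at that time point. Show deaths and withdrawals separately.
- Report completion of the cycling protocol as an adherence measure, intervention arm only, beside session-level fidelity. State whether stopping because out-of-bed mobilisation has begun counts as completion.
- Re-check the Table s8 retention threshold. A value chosen for completing cycling cannot be carried over unexamined to a measure of follow-up.
- Document the change as an amendment made without reference to results by arm. The Abstract says recruitment opened in July 2024, and the Blinding section says research personnel are not blinded.

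The cost is a documented change to a feasibility outcome and a review of one threshold. The assessments are already planned in both arms, so no new data are needed, and the total of 84 stands.

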#### Secondary outcomes

A variety of delirium outcome measures have been selected following guidance from the DelCORS study to explore how delirium can be recorded.^
19
^ Evaluation of these complimentary outcomes will provide important understanding of the methods for characterising delirium for example, duration, severity specifically for patients requiring IMV. These data will contribute towards the selection of the primary outcome measure for a future definitive trial. The timepoints of the listed outcomes are detailed below and Table s7. Please see the separately published statistical analysis plan for details of delirium assessment and analysis of outcomes.

Occurrence of delirium (CAM-ICU, day 0–14, day-30)Delirium free days (CAM-ICU, day 0–14, day-30)Duration (days) of delirium (CAM-ICU, day 0–14, day-30)Severity of delirium (CAM-ICU-7, day 0–14)Physical function (Functional Status Score for the ICU (FSS-ICU), day 14/out-of-bed mobilisation)Time to delirium resolution (number of days)ICU and hospital length of stay (number of days)Ventilator free days (number of days, day 0–30)Sedation free days (number of days, day 0–30)Daily Richmond Agitation Sedation Scale (RASS)Adverse eventsDeaths

### Follow-up

All trial participants will be followed up at 90-days from randomisation. Participants will complete questionnaires measuring quality of life (QoL) and pain (EQ-5D-5L, SF-36), a cognitive screening assessment (MOCA) and assessment of their physical function (6MWT). Their relatives and/or carers will complete a proxy QoL questionnaire (proxy-EQ-5D-5L) and an assessment for the presence of delirium (FAM-CAM).

### Participant timeline

See Figure 2 below for participant flow through the trial.

**Figure 2. fig2-17511437251400612:**
[figure not shown]
Participant flow.

### Blinding

Blinding of participants, research and clinical personnel will not be possible due to the visible nature of the intervention. Analysis of outcome data will be undertaken by the Chief Investigator. The PenCTU will recode participant trial identifiers to ensure analyses are undertaken without knowledge of trial group allocation to reduce any potential bias. Moreover, subjective bias will be minimised by the prospectively published statistical analysis plan and by using standard operating procedures for all trial processes.

## Data collection

Data will be entered into the RedCAP database. Table s7 outlines the timeline of data collection throughout the trial.

### Statistical plan

#### Sample size

The aim of the study is to provide estimated rates of feasibility outcomes (recruitment, retention, fidelity). For a feasibility RCT designed with 80% power and one-sided 5% alpha, a sample size of 58 participants (29 per treatment arm) is recommended.^
22
^ Eighty-four participants will be recruited (42 per group). This will allow for a loss to follow-up due to mortality (up to 30%).^
6
^ This number is based upon recruitment uptake, participant retention and intervention fidelity using a red, amber, green (RAG) system as per best practice guidelines (Table s8) and in consultation with the PenCTU and expert opinion (VA, DM).^
22
^ The RAG system will guide progression to a definitive trial of effectiveness where green (go) and amber (go with changes made) criteria are met. If feasibility criteria are within the red, this means progression to a full trial will only be considered if changes are possible. The RAG criteria have been pre-defined in consultation with expert opinion and will be consulted across the length of the feasibility trial by the key stakeholders (Chief Investigator, PIs, PenCTU, Sponsor, Trial Steering Committee and Trial Management Group).^
23
^ This estimated sample size aims to ensure all areas of uncertainty that is, feasibility measures, are tested and an appropriate sample population for the qualitative study and mechanistic sub-study is achieved.

